# Study protocol of Prednisone in episodic Cluster Headache (PredCH): a randomized, double-blind, placebo-controlled parallel group trial to evaluate the efficacy and safety of oral prednisone as an add-on therapy in the prophylactic treatment of episodic cluster headache with verapamil

**DOI:** 10.1186/1471-2377-13-99

**Published:** 2013-07-28

**Keywords:** Episodic cluster headache, Prednisone, Verapamil, Prophylactic treatment, Clinical trial, Prospective study, Study protocol

## Abstract

**Background:**

Episodic cluster headache (ECH) is a primary headache disorder that severely impairs patient’s quality of life. First-line therapy in the initiation of a prophylactic treatment is verapamil. Due to its delayed onset of efficacy and the necessary slow titration of dosage for tolerability reasons prednisone is frequently added by clinicians to the initial prophylactic treatment of a cluster episode. This treatment strategy is thought to effectively reduce the number and intensity of cluster attacks in the beginning of a cluster episode (before verapamil is effective). This study will assess the efficacy and safety of oral prednisone as an add-on therapy to verapamil and compare it to a monotherapy with verapamil in the initial prophylactic treatment of a cluster episode.

**Methods and design:**

PredCH is a prospective, randomized, double-blind, placebo-controlled trial with parallel study arms. Eligible patients with episodic cluster headache will be randomized to a treatment intervention with prednisone or a placebo arm. The multi-center trial will be conducted in eight German headache clinics that specialize in the treatment of ECH.

**Discussion:**

PredCH is designed to assess whether oral prednisone added to first-line agent verapamil helps reduce the number and intensity of cluster attacks in the beginning of a cluster episode as compared to monotherapy with verapamil.

**Trial registration:**

German Clinical Trials Register DRKS00004716

## Background

Episodic cluster headache (ECH) is a primary headache disorder characterized by intense unilateral attacks of facial and head pain lasting between 15 and 180 minutes accompanied by trigemino-autonomic symptoms. The attacks occur between once every other day and eight times per day for an episode lasting between a week and several months. Headache episodes (“inside bouts”) are followed by symptom-free intervals (“outside bouts”) with duration of at least one month. These episodes follow a circadian and circannual rhythm [1].

Therapy for ECH consists of abortive medication such as high flow oxygen, triptans, analgesics or intranasal lidocaine and prophylactic treatment to reduce the number of attacks and quickly end the bout, e.g. verapamil, topiramate or lithium [2-4].

Amongst these, verapamil is regarded as the drug of choice by national and international therapy guidelines. In Germany verapamil is recommended by the “Gemeinsamer Bundesausschuss” (“Federal Joint Committee”) as an off-label-indication (meaning that the treatment is reimbursed by the sick funds). Verapamil has shown efficacy in some randomized controlled studies [5]. Due to its delayed onset of efficacy of usually 10 to 14 days and the required slow titration of the dose to increase tolerability, guidelines recommend initiating short-term prophylactic treatment with overlapping prednisone administration [2-4].

### Rationale for a phase III trial

Studies investigating the efficacy of prednisone in ECH do not yet provide clear evidence in favor of this therapy [6-12]. While several small studies concluded that there is no prednisone effect in ECH patients [6,13-15], other studies suggested that prednisone has an effect in reducing the number of attacks and even terminating the bout [7,9,11]. In a non-randomized trial, 14 ECH patients were administered 250 mg methylprednisolone I.V. over the course of five days followed by a slow tapering of the dosage. Three patients reported immediate relief after the first dose, while ten reported a cessation of cluster attacks after 3.8 (+/− 2.2) days (10).

Since the evidence regarding efficacy and safety of prednisone in the initial treatment of ECH is so limited, ECH patients often suffer from the delayed initiation of a treatment intervention. This trial will provide phase III evidence regarding efficacy and safety of oral prednisone added to first-line agent verapamil in the beginning of a cluster headache episode as compared to monotherapy with verapamil. Furthermore, this trial will also provide evidence regarding long-term outcomes in ECH-patients after prednisone administration.

### Alternative treatment options

Lithium is the only agent approved for the prophylactic treatment of ECH (dosage between 600 mg and 1500 mg/d), despite the lack of a controlled clinical trial [16]. Lithium requires regular plasma concentration and laboratory monitoring due to its various side effects [17]. Therefore it is mentioned in both German and international treatment guidelines only as the 2nd choice when therapy with verapamil fails or if there are contraindications for the use of verapamil. Verapamil is the only substance that was tested in a controlled clinical trial following current standards for evidence-based medicine [5].

Other second-line agents with unproven efficacy in ECH are: pizotifen, methysergide, valproic acid, topiramate, melatonin and gabapentin [18-26]. These substances are used in an off-label-indication. There are no data regarding prophylactic therapy of ECH using triptans on a daily basis: while sumatriptan (100 mg/d) showed no effect on the long term outcome, naratriptan (2,5 – 5 mg/d) and eletriptan (40 mg/d) led to a significant reduction of attack frequency [27-29].

Another treatment option is the local infiltration of the greater occipital nerve with local anesthetics and steroids [30-32]. Two randomized-controlled trials reported a significant reduction in the number of cluster attacks after suboccipital injection of corticosteroid preparations targeting the greater occipital nerve [33,34]. There is no evidence yet as to which corticosteroid preparation, what form of application, or which dosage is the most efficient in the treatment of ECH.

## Methods and design

### Design

PredCH is a prospective, randomized, double-blind, placebo-controlled trial with two parallel interventional arms: all eligible patients with ECH will receive verapamil and will then be 1:1 randomized to the treatment intervention with prednisone or placebo. This multi-center study is being conducted at eight German sites specializing in headache treatment, and aims to recruit a total of 144 patients (see section on sample size calculation below).

### Primary objective

The primary objective of this trial is to assess whether prednisone can reduce the total number of cluster attacks within the first week of treatment compared to a placebo, as documented by the patients in their headache diary. This endpoint follows the “Guidelines for controlled trials of drugs in cluster headache” of the International Headache Society and has been used in previous trials on ECH treatment.

### Secondary objectives

PredCH will also assess the effect of ± prednisone for the following secondary endpoints:

1. Number of cluster attacks from day 1 to day 28 of study participation.

2. Number of cluster attacks from day 7 to day 28 of study participation.

3. Episode abortion (yes/no), defined as no further attacks in the last 3 days before follow-up on day 7 or day 28.

4. Acute medication intake up till day 7; up till day 28.

5. Responder rate (defined as a reduction in the number of daily attacks >50% measured after 7 and 28 days as compared to mean number of attack during the last three days before inclusion).

6. Presence or absence of trigemino-autonomic symptoms (yes/no) after 7 and 28 days:

a) Lacrimation

b) Nasal congestion, rhino rhea

c) Conjunctival injection

d) Ptosis

e) Miosis

f) Facial sweating on side of pain

7. Impact on quality of life, assessed on day −1 and day 28:

a. SF-12 [34]

b. HIT-6 [35]

c. ADS [36]

8. Pain intensity (mean) of cluster attacks in the first seven days and the first 28 days after initial treatment as measured by the Numerical Rating Scale.

9. Tolerability and safety

a. Adverse events, pathological findings on neurological and medical examination, urinary and blood tests, ECG changes.

b. Drug accountability check on day 7 and day 28

c. CGI [37] on day 7 and day 28, compared to baseline.

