### Visit 0 (baseline)

The study patient will be randomized and study medication will be handed out. The headache diary will be explained to the patient. Screening and randomization can take place on the same day.

### Visit 1

Visit 1 will take place seven days after the baseline visit. A standardized interview will be performed as well as a medical and neurological examination. ECG and vital parameters will be documented. Therapy compliance and the headache diary will be controlled and headache frequency evaluated. Adverse events and dropouts from the study will be documented.

### Visit 2

Visit 2 will be performed 28 days after inclusion. In addition to the tests performed in visit 1, impairment of quality of life will be reassessed (HIT-6, ADS and SF-12) and blood tests will be performed in order to evaluate safety.

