### Eligibility

#### Inclusion criteria

Male and female patients between 18 and 65 years of age, of legal competence, with sufficient knowledge of written and spoken German, capable of attending regular follow-up visits.

Episodic cluster headache according to the IHS-criteria; patient has had at least one previous episode (bout) before; average duration of previous cluster episodes should have been at least one month; expected duration of cluster period after randomization should be at least one month after initiation of therapy; previous cluster episodes should have ended at least one month prior to inclusion; beginning of ongoing bout of cluster headache should be less than 30 days ago.

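### The fixed three-day baseline for the responder rate reaches back before the bout in patients enrolled one or two days after onset, so their >50% rule becomes about >83% or >67%

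*Protocol article*

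**What the plan says.** Protocol article, Secondary objectives, item 5: "Responder rate (defined as a reduction in the number of daily attacks >50% measured after 7 and 28 days", with the reference value given as "compared to mean number of attack during the last three days before inclusion". The window always has three days.

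Protocol article, Inclusion criteria: for the current bout, "beginning of ongoing bout of cluster headache should be less than 30 days ago". This is an upper limit only. For earlier bouts, "previous cluster episodes should have ended at least one month prior to inclusion", so the days just before the current bout are expected to be free of attacks. The diagnostic criterion, "Episodic cluster headache according to the IHS-criteria", asks for no attack count in the three days before entry.

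Protocol article, Visit 0 (baseline): "Screening and randomization can take place on the same day". The diary is introduced at the same visit. Nothing therefore guarantees three in-bout days before inclusion.

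Protocol article, Efficacy: the primary endpoint is the attack count in week one, modelled with sex, age group and site. Secondary endpoints are exploratory, with details left to an analysis plan.

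**The concern.** A percentage reduction means what it says only if both rates describe the same state, here an active bout. The trial aims at the start of an episode and admits patients from the first day of a bout. For someone entered one or two days after onset, part of the baseline window lies in the symptom-free interval. The baseline rate is too low and the bar for response is too high.

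For example, suppose attacks run at 3 per day and fall to 1 per day, a true reduction of 67%. If the bout began one day before inclusion, the window holds 3 attacks over 3 days, a baseline of 1 per day. The measured reduction is 0% and the patient counts as a non-responder.

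At stake is what the responder rate means for the earliest-enrolled patients, and some loss of contrast between the arms on that endpoint.

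**Working it through.** **The plan's own figure.** No figure is given for the responder endpoint. The primary sample size reproduces: difference 2.5, SD 4.2, two-sided α 0.05 and power 0.9 give 60.3 per arm by t-test, rounded up to 61, so 122. Then 122 / 0.85 = 143.5, rounded up to 144. Endpoint 5 plays no part in it.

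**Threshold.** Let r be the in-bout daily rate and k the number of baseline days inside the bout. The measured baseline is (k/3)·r. A patient is scored a responder if the follow-up rate is below 0.5·(k/3)·r, so the true reduction must exceed 1 − k/6:

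- k = 3: more than 50%
- k = 2: more than 66.7%
- k = 1: more than 83.3%

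**Per-patient effect, simulated.** Inputs from Sample size and power: 8.25 attacks per 5 days (1.65 per day), SD 4.2. Assumptions: gamma-Poisson counts with shape 8.25² / (4.2² − 8.25) = 7.25, follow-up taken as the mean over days 1 to 7, and a zero baseline counted as not a responder.

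| In-bout days | Zero baseline | Scored responder, true 60% reduction: fixed divisor | same, in-bout divisor | Scored responder, no change: fixed divisor | same, in-bout divisor |
|---|---|---|---|---|---|
| 3 | 2% | 62% | 62% | 9% | 9% |
| 2 | 7% | 40% | 59% | 3% | 11% |
| 1 | 23% | 16% | 54% | 1% | 15% |

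The gap between a true 60% reduction and no change is 53 points with a full window. With two in-bout days it is 36 points under the fixed divisor and 48 under the in-bout divisor. With one day it is 16 and 39. If attacks stop completely, every patient with a non-zero baseline is scored a responder under either rule.

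**How many patients.** The distribution of bout age at inclusion is not stated. If it were uniform over days 1 to 29, 2/29 = 6.9%, about 10 of 144, would have a truncated window. Uniform over days 0 to 29 gives 3/30 = 10%, about 14 of 144. A share between 2% and 20% would be about 3 to 29 patients.

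**Overall effect at a true 60% reduction, uniform over days 1 to 29.** (27 × 0.622 + 0.397 + 0.164) / 29 = 0.598, against 0.622 with full windows: a loss of about 2 points. With the in-bout divisor, (27 × 0.622 + 0.592 + 0.537) / 29 = 0.618. If day-0 patients are added, they have no in-bout day and cannot be scored. Leaving them out keeps the loss at about 2 points. Counting them as non-responders makes it about 4 (17.355 / 30 = 0.579), and neither divisor rescues them.

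**The case against.** The strongest reply is that this is small. Endpoint 5 is one of nine secondary items, all exploratory. The primary count uses no baseline. Truncation is fixed before randomization, so it falls on both arms alike in expectation; it weakens the responder contrast rather than favouring an arm. All of that stands and sets the priority.

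A second reply is that the repair trades one error for another, because a rate from one or two days is noisy. That stands in part: no-change patients scored as responders rise from 9% with three days to 11% with two and 15% with one (19% with one day among those with at least one attack). The gain in true responders is larger, as the gaps above show.

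Several stronger readings are tempting but not supported:

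- That a patient one or two days into a bout is the typical entrant. No bout-age distribution is given, and under the uniform assumption at least 90% have a full window.
- That true responders are lost in general. The loss falls mainly on true reductions between 50% and 67% (two days) or 50% and 83% (one day).
- That empty baselines are common. The Background says "The attacks occur between once every other day and eight times per day". At the lowest rate a three-day window is empty in exp(−1.5) = 22% if attacks are Poisson, but in 0% if they come strictly every other day. At the plan's mean rate a full window is empty in 0.7% (Poisson) to 2.3% (gamma-Poisson). How to score these few is an ordinary analysis-plan convention.
- That an attack-free entrant already counts as an episode abortion. Item 3 is "defined as no further attacks in the last 3 days before follow-up on day 7 or day 28", so it cannot be met before treatment.
- That the same value distorts other analyses. The document shows no other use of it.

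**Conclusion.** The point holds as a limited defect in a stated definition. With no minimum bout age and no run-in, the fixed three-day divisor turns the stated >50% rule into about >67% or >83% for patients with two or one in-bout days, and partial responders among them are under-scored. The thresholds are exact arithmetic. The scored proportions rest on the gamma-Poisson model and a 7-day follow-up mean; the 7 to 10% affected and the shift of about 2 points rest on uniform bout age. An analysis plan might refine the rule, but the divisor is already fixed in the protocol, so this is more than an omitted detail. The primary endpoint, the sample size and the other secondary endpoints are unaffected. Priority: CONSIDER.

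**What to change.** In Secondary objectives, item 5, define the baseline as the attacks in the last three days before inclusion divided by the number of those days (1, 2 or 3) that lie in the current bout, counted from bout onset. Onset already has to be established to check the under-30-days criterion, so no new measurement is needed, provided the date is recorded.

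The cost is one sentence in the endpoint definition, plus the noisier short baselines. Under the uniform days 1 to 29 assumption, the share of no-change patients scored as responders moves from (27 × 0.0925 + 0.033 + 0.008) / 29 = 8.8% to (27 × 0.0925 + 0.111 + 0.148) / 29 = 9.5%. Repeating the endpoint in patients with three in-bout days would show whether the short baselines matter. The scoring of a zero baseline can be left to the analysis plan.

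A new inclusion criterion, such as a minimum attack count before entry, is not needed: it would change the trial population for one exploratory endpoint, and the primary count does not require it.

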### Interventions

Patients in the active add-on treatment arm (treatment intervention) are administered oral prednisone as an add-on therapy to the prophylactic treatment with verapamil. Administration accords to Table 1. The dosing regimen is adapted from international treatment guidelines [2-4].

**Table 1 T1:** Dosing scheme of prednisone/placebo

Day 1 – 5	100 mg (5× 20 mg) prednisone/placebo P.O. once daily
Day 6 – 8	80 mg (4× 20 mg) prednisone/placebo P.O. once daily
Day 9 – 11	60 mg (3× 20 mg) prednisone/placebo P.O. once daily
Day 12 –14	40 mg (2× 20 mg) prednisone/placebo P.O. once daily
Day 15 – 17	20 mg (1× 20 mg) prednisone/placebo P.O. once daily

Patients in the placebo arm will receive placebo capsules P.O. (Table 1) as an add-on therapy to the prophylactic treatment with verapamil. Both groups will also receive potassium substitution and pantoprazole 40 mg daily.

Patients in both groups are allowed to use their regular analgesic medication for acute attacks (see also “additional pain medication”) and will receive the basic and additional therapy described below.

Compliance is controlled and documented on day 7 and day 28. In case of a medical emergency the arms can be unblinded.

Prednisone and placebo capsules are produced for this clinical trial at the pharmacy of the University of Heidelberg.

### Basic therapy

In addition to prednisone or a placebo, each patient will be prescribed the standard prophylactic therapy with verapamil P.O., starting on the first day of study participation and following the dosing scheme in Table 2.

**Table 2 T2:** Dosing scheme of verapamil

Day 1 – 3	40 mg - 40 mg - 40 mg
Day 4 – 6	40 mg - 40 mg - 80 mg
Day 7 – 9	40 mg - 80 mg - 80 mg
Day 10 – 12	80 mg - 80 mg - 80 mg
Day 13 – 15	80 mg - 80 mg - 120 mg
Day 16 – 18	80 mg - 120 mg - 120 mg
Day 19 – end of trial	120 mg - 120 mg - 120 mg

If a patient experiences intolerance or adverse effects due to verapamil before reaching the target dosage of 360 mg daily, lower tolerable doses can be continued.

### Additional therapy

Oral potassium (as an effervescent tablet) 1,56 g/d and pantoprazole 40 mg/d P.O. will be prescribed to prevent prednisone side effects such as gastric ulcer and hypokalemia.

### Additional pain medication

The following drugs and maximal daily doses will be allowed:

NSAID: Ibuprofen 800 mg/d; aspirin 500 mg/d; diclofenac 50 mg/d; naproxen 250 mg/d paracetamol 1000 mg/d; metamizole 2000 mg/d. Mixed analgesics: i.e.Thomapyrin (acetylsalicylic acid 250 mg, paracetamol 200 mg and caffeine 50 mg) 1 tablet per day.

Triptans: almotriptan 2× 12,5 mg/d; eletriptan 2× 40 mg/d; rizatriptan 2× 10 mg/d; frovatriptan 2× 2,5 mg/d; naratriptan 2× 2,5 mg/d; sumatriptan 2× 100 mg/d P.O.; 2× 20 mg/d nasal; 2× 6 mg/d SQ; zolmitriptan 2 × 5 mg P.O.; 2× 5 mg nasal.

Ergotamine 2× 2 mg/d P.O.

Lidocaine (4%) nasal 0,5 ml/d.

High flow (6–12 l/min) inhalation of 100% oxygen.

### Estimated timeline

Recruitment will begin in April 2013 and end in March 2015.

### General structure of the study

The duration of the study for each patient is 28 days (including 17 days of treatment/placebo intervention). It consists of 4 visits (see Figure 1) including a screening visit, a randomization visit, and two follow-up visits during which therapy response, safety, and compliance will be assessed.

**Figure 1 F1:**
[figure not shown]
Visit scheme of PredCH (will be provided as separate file).

### Screening visit (“visit −1”)

The screening visit consists of a standardized interview, assessment of eligibility and informed consent. Impairment by ECH is measured with three instruments, evaluating quality of life (SF-12), depression (ADS) and severity of headache (HIT-6). Medical and neurological exams are performed and an ECG and vital parameters are obtained prior to verapamil administration. Urine and blood samples are obtained in order to screen for diabetes, electrolyte disturbances and ongoing systemic infection (e.g. acute urinary tract infection) prior to prednisone therapy. Female patients will also be screened for pregnancy.

### Visit 0 (baseline)

The study patient will be randomized and study medication will be handed out. The headache diary will be explained to the patient. Screening and randomization can take place on the same day.

### Visit 1

Visit 1 will take place seven days after the baseline visit. A standardized interview will be performed as well as a medical and neurological examination. ECG and vital parameters will be documented. Therapy compliance and the headache diary will be controlled and headache frequency evaluated. Adverse events and dropouts from the study will be documented.

### Visit 2

Visit 2 will be performed 28 days after inclusion. In addition to the tests performed in visit 1, impairment of quality of life will be reassessed (HIT-6, ADS and SF-12) and blood tests will be performed in order to evaluate safety.

### Randomization/stratification

Randomization will be conducted using a web-based tool “TenALEA”. Patients will be stratified at randomization according to age (<30 years vs. ≥30 years), sex and participating site.

### Eligibility

#### Inclusion criteria

Male and female patients between 18 and 65 years of age, of legal competence, with sufficient knowledge of written and spoken German, capable of attending regular follow-up visits.

Episodic cluster headache according to the IHS-criteria; patient has had at least one previous episode (bout) before; average duration of previous cluster episodes should have been at least one month; expected duration of cluster period after randomization should be at least one month after initiation of therapy; previous cluster episodes should have ended at least one month prior to inclusion; beginning of ongoing bout of cluster headache should be less than 30 days ago.

